## Abstract

Supplemental Digital Content is available in the text

## Introduction

1

Gastric carcinoma (GC) is the fifth malignancy and the third cause of cancer death worldwide, and colorectal carcinoma (CRC) is the third most common fatal cancer worldwide.^[1,2]^ The curative treatment for non-early GC and CRC is mainly surgical, and the treatment for advanced GC and CRC is a multimodal treatment model based on chemotherapy. Due to the several phase III studies showing the treatment benefits of neoadjuvant and adjuvant chemotherapy protocols, there have been major advances in the multimodal treatment of GC and CRC.^[3–5]^ Although the total effective rate of first-line and second-line chemotherapy is better than before, the prognosis of GC and CRC still needs to be improved.

Maintenance therapy refers to the mode that patients with advanced cancer who have been given by drug treatment and have their condition under control will stop the original treatment plan and switch to other plans for the next treatment until the disease progresses. In some studies on maintenance therapy for GC, patients without progression after firstline chemotherapy that include docetaxel, cisplatin and XELOX were randomly assigned to receive capecitabine maintenance. The results showed that the median progression-free survival (PFS) and median overall survival time (OS) of the patients receiving maintenance therapy were significantly better than that of the group without maintenance therapy, and grade 3/4 adverse events (AEs) and hematological toxicity were less common during maintenance therapy.^[6,7]^ The same result has also been found in GC studies where the targeted drug trastuzumab was selected as maintenance therapy.^[8]^ These studies suggest that maintenance therapy may benefit patients with advanced GC after chemotherapy, but more research is needed in this regard.

The maintenance therapy of advanced CRC is more mature than that of GC. During the past decade, capecitabine or capecitabine combined with bevacizumab has been repeatedly used in maintenance therapy after first-line chemotherapy studies for advanced CRC, and the results showed that the PFS and OS of the maintenance group were improved compared with the control group.^[9–11]^ The evidence shows that the use of fluorouracil or targeted drugs in the maintenance therapy of advanced CRC can benefit the survival of patients, which preliminarily proves that the maintenance model is feasible in the treatment of patients with advanced CRC.

Capecitabine has been widely used as an oral fluorouracil chemotherapeutical drug in chemotherapy for GC and CRC, and the new oral fluoropyrimidine S-1 was developed by Japan; studies have shown that it may be more suitable for Asians. It is a compound preparation whose main components are tegafur, gimeracil, and potassium oxonate, tegafur acts as a prodrug of 5-fluorouracil (5-FU), gimeracil maintains the serum concentration of 5-FU, and potassium oxonate inhibits the phosphorylation of 5-FU in the gastrointestinal tract to potentially decrease serious gastrointestinal toxicities. At present, S-1 is widely used as the adjuvant and palliative chemotherapy for GC and CRC.^[12–16]^

Now many studies have shown that the application of traditional Chinese medicine (TCM) can significantly reduce the adverse reactions caused by chemotherapy, improve postoperative maintenance, prevent recurrence and metastasis, enhance patient quality of life, and prolong survival.^[17–20]^ XiangshaLiujunzi Decoction (XSLJZD)^[21–24]^ is a classic TCM formula containing 8 commonly used herbs (Radix codonopsis, Rhizoma atractylodis macrocephalae, Radix glycyrrhizae, Poria, Pericarpium citri reticulatae, Pinellia tuber, Radix aucklandiae, and Fructus amomi). With effects of invigorating the spleen and replenishing qi, XSLJZD has long been used to treat gastrointestinal discomfort in clinical practice in China, including those caused by chemotherapy. The use of TCM for tumor maintenance therapy is still inception, but it is gratifying that these preliminary exploratory studies have given some hope to this new clinical treatment model. Tong et al used the modified XSLJZD combined XELOX scheme in treatment of the advanced GC, and found that the modified XSLJZD alleviates the adverse reactions of XELOX chemotherapy and improves the quality of life and immunity as well as the therapy effects in the patients with advanced GC.^[25]^

In recent years, the maintenance therapy mode of lung cancer has become more mature, and there is still room for gastrointestinal tumors to develop. Besides, there has no report on maintenance therapy mode of combination of chemotherapeutic drugs with TCM. Therefore, this study will aim to combine the research foundation of the preliminary small-scale exploratory trials to carry out a randomized, controlled trial for further evaluation of the efficacy and safety S-1 combined with XSLJZD in the maintenance therapy of stage III or IV GC and CRC.

## Methods and analysis

2

### Study design

2.1

This study is an open, single-center, randomized controlled trial (RCT), wherein 256 patients with stage III or IV GC and CRC (128 patients of each carcinoma type) who met the inclusion criteria will be randomly assigned to 2 groups, receiving S-1 or S-1 combined with XSLJZD for 5 years. The flowchart of the study is presented in Figure 1.

**Figure 1 F1:**
[figure not shown]
The flowchart of the study.

The reporting of the protocol follows the Standard Protocol Items: Recommendations for Interventional Trials 2013 (SPIRIT2013) guidelines.^[26,27]^

### Recruitment

2.2

The study was carried out at the Oncology Center of the Affiliated Hospital of Guangdong Medical University. The participants were all inpatients of the Oncology Center of Affiliated Hospital of Guangdong Medical University, mainly recruited through Internet advertisements and hospital posters. The patients interested in participating in the study will be evaluated by clinicians to determine their qualifications. The clinician will inform the patient of the detailed study objectives, process, and potential benefits and risks. All participants will sign the informed consent before screening.

### Inclusion criteria

2.3

Patients will be enrolled in this trial if they meet the following criteria: there must be an informed consent form signed by the patient himself or by the witness; TNM III-IV GC or CRC; controlled by chemotherapy (CR/PR/SD); age 18 to 75 years (≥18 years’ old, ≤75 years’ old), expected survival period is >3 months; KPS ≥60^[28]^; follow the Response Evaluation Criteria In Solid Tumors (RECIST 1.1),^[29]^ at least 1 measurable lesion; routine blood test: hemoglobin ≥90 g/L; neutrophil count ≥1.5 × 10^9^ cells/L; platelet count ≥100 × 10^9^ cells/L; biochemical examination: total bilirubin ≤1.5 × upper limit of normal range (ULN), alanine aminotransferase (ALT) and aspartate aminotransferase (AST) ≤2× ULN, if liver metastasis, ALT and AST ≤5× ULN, endogenous creatinine clearance rate ≥60 mL/min; cardiopulmonary function is basically normal.

### Exclusion criteria

2.4

Patients meeting the following criteria will be excluded: patients with severe heart, liver, or kidney damage or abnormal bone marrow function; past or concurrent with other malignant tumors, except for cured skin basal cell carcinoma and cervical carcinoma in situ; the general situation is poor, and those who cannot eat Chinese medicine; According to the judgment of the investigator, serious accompanying diseases that endanger the safety of the patient or affect the patient's completion of the study; pregnant or lactating women; people who are known to be allergic to the therapeutic drugs used in the trial.

### Ethics approval

2.5

Ethics approval has been done by the Ethics Committee of the Affiliated Hospital of Guangdong Medical University (YJ2016-010KT-01). Information on any AE will be reported to the Ethics Committee a stable situation is reached. Moreover, the Ethics Committee has the duty to evaluate the progress of this study periodically.

### Randomization and blinding

2.6

According to the random number generated by the computer, the drugs corresponding to the randomly assigned drug number are given in the order of participants’ enrollment. Participants who meet the eligibility criteria will be randomly assigned to the S-1 group and S-1 combined with XSLJZD group in a 1:1 ratio. Clinicians, patients, data collectors, and outcome assessors will be blinded to the group assignment. The allocation will be unblended if a severe adverse event (SAE) occurs and when the final data analysis is complete.

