#### Other measurements

2.8.3

Baseline was defined as pre chemotherapy (−7 to 0 days). During baseline examination, the patient's gender, age, marital status, education level, comorbidity, pathological type, tumor staging, radiotherapy and chemotherapy regimen, and medication records for the past 3 months will be recorded.

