### Sample size estimate

2.12

The RCT is an advantage test that uses an appropriate formula to estimate the sample size. Based on the results of our preliminary observational study and expert advice, we assume a significant level of α = 0.05, test efficacy (1-β) = 80%, and a pooled standard deviation of 9.59. Considering 10% dropout rate, the total sample size is expected to be 256 (128 of each carcinoma type, 64 in each group).

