### Statistical analysis

2.13

Analysis for primary endpoint PFS and secondary endpoint OS: the median of PFS and OS in each group was counted. Survival curves were plotted using Log-Rank test and Kaplan–Meier survival analysis.

Analysis for Symptom Improvement Assessment: behavioral status scores before and after chemotherapy (KPS), repeated measure's analysis of variance before and after treatment in the group; TCM symptom scores before and after chemotherapy (MDASI-TCM), paired *t* test before and after treatment in the group. The *t* test was used for comparison between groups.

All these statistical analyses were performed with SPSS 23.0 (SPSS Inc, Chicago, IL). A 2-tailed *P* value <.05 was considered statistically significant.

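### The allocation described does not secure 64 per arm within each cancer type, and the log-rank test on PFS names no strata and is not fixed as pooled or per type

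*Protocol article*

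**What the plan says.** - **Allocation (section 2.6).** Computer-generated random numbers are used, and "the drugs corresponding to the randomly assigned drug number are given in the order of" enrolment, 1:1 to two arms. No stratification factor, block scheme or separate list by cancer is named.
- **Target split (section 2.12).** The total of 256 is broken down as "128 of each carcinoma type, 64 in each group". Section 2.1 repeats the quota of 128 per cancer.
- **Population (section 2.3).** Stages III and IV are eligible for both cancers. There is no quota by stage.
- **Primary analysis (section 2.13).** For PFS, "the median of PFS and OS in each group was counted", with Kaplan–Meier curves and a log-rank test, two-sided at 0.05. No stratum is named, and it is not said whether the comparison is made across both cancers or within each.
- **Baseline data (section 2.8.3).** The recorded items include "pathological type, tumor staging".
- **Setting (section 2.1).** The trial is described as open and single-centre.

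**The concern.** The sample-size section fixes an arm size within each cancer, but the allocation described takes no account of cancer type. The split therefore arises only by chance.

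The comparison of PFS then brings together patients who may differ in prognosis by cancer and by stage. If they are pooled in an unstratified log-rank test, the marginal HR moves toward 1 and power can fall. If each cancer is tested on its own, as the per-type sizing suggests, stages are still mixed within each test, and there are two tests at 0.05 with no stated rule for reading them together. The document does not settle which of these is the primary comparison.

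**Working it through.** **1. The plan's own figure.** The stated inputs are "we assume a significant level of α = 0.05", "test efficacy (1-β) = 80"%, "a pooled standard deviation of 9.59" and "Considering 10% dropout rate". No difference to detect, HR, median PFS or event count is given, so 64 per arm cannot be reproduced from them. Solving backwards with the two-means formula n = 2[SD(1.960 + 0.842)/δ]², an assumed δ = 5 gives n = 57.75 per arm, and 57.75/0.9 = 64.2. So 64 per arm fits a comparison of means at about δ = 5. The document states no PFS power from which a loss could be measured.

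**2. Does the described allocation give 64:64 within a type?** Take 128 patients of one type.

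| Scheme (assumed) | Exactly 64:64 | 95% range, one arm | 58:70 or worse |
|---|---|---|---|
| Simple randomisation, Binomial(128, 0.5) | 7.0% | 53–75 | 33% |
| One list balanced 128:128 overall, Hypergeometric(256, 128, 128) | 9.9% | 56–72 | 17% |

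Blocks of 4 in a single list that ignores type give about 10% and the same 56–72.

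**3. What does the imbalance itself cost?** Per type, 128 × 0.9 ≈ 115 events if all retained patients have an event (assumed). Power = Φ(√[D·p(1 − p)]·|ln HR| − 1.960). At an assumed HR of 0.59:
- p = 64/128: √(115 × 0.2500) × 0.5276 − 1.960 = 0.869, so 80.8%.
- p = 53/128: √(115 × 0.2426) × 0.5276 − 1.960 = 0.827, so 79.6%.

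The cost is about 1 point.

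**4. What does a pooled, unstratified test cost?** Pooled events are 256 × 0.9 ≈ 230. The HR giving 80% power is exp(−2 × 2.802/√230) = 0.69, which is used as the assumed effect. The main simulation has 256 patients, equal stage mix, median PFS 6 months, 10% early censoring, 3,000 runs per setting and an unstratified list. All of these are assumptions.

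| Prognostic HR: type, stage | Unstratified | Stratified by type × stage | Loss (points) |
|---|---|---|---|
| 1, 1 | 81.3% | 78.4% | −2.9 (a gain) |
| 1.3, 1.3 | 78.5% | 78.5% | 0 |
| 1.5, 1.5 | 75.3% | 78.5% | 3.2 |
| 1.5, 2 | 72.1% | 78.2% | 6.1 |
| 2, 2 | 66.6% | 78.3% | 11.7 |
| 2, 3 | 60.2% | 78.2% | 18.0 |

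A second simulation at HR 0.69 gave, unstratified against stratified, 77% v 76% with no spread, 73% v 76% at 1.5 and 1.5, 66% v 75% at 2 and 2, and 51% v 74% at 2 and 4.

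**5. Attenuation.** With a true HR of 0.69 and assumed type medians of 5 and 10 months, the unstratified HR averages about 0.71.

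**6. Validity.** With no treatment effect, the unstratified test rejected in 4.7–5.1% of trials under the unstratified list, and in 3.6–4.4% under stratified randomisation (prognostic HRs of 1.5 and 1.5, and 2 and 2).

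**7. Where the gain comes from.** With the stratified test, moving from an unstratified to a stratified list changes power by about −1 to +2 points. Nearly all the gain comes from the test.

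**8. If each type is tested separately at 0.05.** 1 − 0.95² = 9.75% chance of at least one false positive when neither treatment effect is real.

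**The case against.** The strongest reply is that much of this is read from silence. Section 2.6 does not say that there is a single list; order of enrolment is compatible with one list per cancer, and the quotas could suggest it. Section 2.13 does not say that the test is pooled or that it is unstratified. A condensed article often leaves blocks, strata and the exact form of the test to a full protocol or analysis plan that is not shown.

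That stands in part. A single list and a pooled test are the plain reading, because the only groups defined are the two treatment arms, but neither is stated. What remains is that the article describes an allocation method and, separately, a within-type split which that method as described does not deliver. It also sizes by type without saying whether the primary comparison is by type.

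Two stronger inferences are tempting and are not supported:
- **That PFS power is definitely lost.** The documents give no prognostic HR, PFS median or stage mix. With mild spread the loss is nil, and with none the unstratified test does slightly better. The imbalance in arm sizes costs about 1 point.
- **That chance imbalance undermines the test.** Under randomisation the unstratified log-rank keeps its type I error. Imbalance in type or stage can shift the estimate in one trial, but it is not a systematic bias.

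The 9.75% likewise applies only if both per-type tests are primary and uncorrected, which the article does not say.

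**Conclusion.** The concern holds in a limited form. The allocation in section 2.6 does not secure the split in section 2.12: exactly 64:64 within a type would occur in about 7–10% of trials, with a 95% range for one arm of 53–75 (simple randomisation) or 56–72 (one list balanced overall). Section 2.13 leaves the primary comparison undefined as pooled or per type and names no strata.

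If it is pooled and unstratified, the test is valid but the HR is attenuated. The power loss depends on unknown spread: roughly 0 points with little spread, 3–4 at prognostic HRs of 1.5 for both factors, about 10 at 2 and 2, and over 20 only under extreme spread (2 and 4). These figures rest on an assumed HR of 0.69 in 256 patients. The loss comes from the form of the test, not from the allocation. A reader might infer that the trial is underpowered for PFS because of this point; the documents give no basis for saying so. The change is still worth making, because it protects against a possible material loss at very small cost.

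**What to change.** 1. **Section 2.6.** Stratify the randomisation by carcinoma type, and by stage III/IV if feasible. Use varying block sizes, because section 2.1 calls the trial open and it runs at one centre, where fixed blocks could be guessed.
2. **Section 2.13.** State that PFS is compared by a log-rank test stratified by the carcinoma type and stage recorded at baseline, with a stratified Cox HR and 95% CI.
3. **Section 2.13.** State whether the primary comparison is pooled or per type. If it is per type, stratify each test by stage and say how the two 0.05 tests are handled.
4. **If enrolment has begun.** Stratifying the analysis alone recovers nearly all of the power gain. It does not restore the 64:64 split, so section 2.12 should then describe that split as approximate.

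Cost: two lists (four with stage) if a single list is now used, and a few sentences. No new data are needed. If type and stage turn out not to be prognostic, the stratified test gives up about 1 to 3 points of power in the simulations above.

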## Protocol monitoring

3

An independent Response Evaluation Committee (IREC) was in place throughout the trial to monitored the study, which consists of 2 oncology imaging diagnostic and evaluation experts and one oncology clinical expert. Under the premise of blindness, the IREC carries out an independent third-party evaluation of the objective imaging data form all participants. The final was based on the evaluation of IREC. The participants of the clinical study will be informed that there will be relevant personnel to check during the study, but the privacy and data of the patients will be exactly protected. During the clinical study, clinical inspectors will conduct regular on-site monitoring visits to ensure that all content of the research protocol is strictly observed, and the original data are checked to ensure consistency with the CRF.

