Based on the above consideration, we designed the study of XSLJZD combined with S-1 in the maintenance therapy of stage III or IV GC and CRC. It is an open, single-center, and randomized trial, which aims to determine the efficacy and safety of S-1 combined with XSLJZD in the maintenance therapy of stage III or IV GC and CRC. In addition, this study also provides meaningful clinical information for this combination model of chemotherapeutic drugs and TCM, laying the foundation for larger clinical trials in the future. However, the study has several limitations. First, this is a single-center trial, which is more difficult to recruit than multicenter trials. Therefore, it will take longer to recruit if enough samples are recruited. Second, although TCM formulas have been widely used in clinical practice in China, RCT with a well-designed and long-term follow-up is still lacking. Consequently, the results of the RCT will provide experience and evidence for developing guidelines and policies for facilitating the reasonable use of TCM formulas. We also hope that this research will open a new direction for the treatment of patients with stage III or IV GC and CRC.

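### Section 2.6 claims blinding of patients and clinicians, but the protocol twice calls the trial open and describes no masking of the added decoction

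*Protocol article*

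**What the plan says.** The protocol article makes two incompatible statements about blinding.

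- Section 2.1 (Study design): "This study is an open, single-center, randomized controlled trial (RCT". The Discussion repeats it: "It is an open, single-center, and randomized trial".
- Section 2.6 (Randomization and blinding): "Clinicians, patients, data collectors, and outcome assessors will be blinded to the group assignment". It adds a rule that makes sense only if a blind exists: "The allocation will be unblended if a severe adverse event (SAE) occurs and when the final data analysis is complete".

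The arms are described in section 2.1 as "receiving S-1 or S-1 combined with XSLJZD for 5 years". Section 2.7 (Interventions) gives both arms the same S-1 regimen. It adds an eight-herb decoction in one arm, given according to each patient's syndromes. No placebo, sham or matching preparation is mentioned.

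Section 3 (Protocol monitoring) describes a separate safeguard: "Under the premise of blindness, the IREC carries out an independent third-party evaluation of the objective imaging data form all participants". A further sentence there, with a word apparently missing, makes the committee's evaluation the basis of the final assessment.

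**The concern.** A trial that is open to patients and clinicians cannot also blind them, so one of the two statements must be wrong. The one that conflicts with the described treatments is the blinding claim in 2.6.

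What is at stake is mainly the secondary outcomes in section 2.8.2. Pain, fatigue, sleep and similar symptoms come from the patient's own account. KPS and the grading of nausea or neuritis involve clinical judgement. All are assessed before each cycle, and section 2.13 compares scores between groups by *t* test. Patients who know they receive the decoction, and clinicians who give it expecting it to relieve symptoms, can shift such scores without any true effect. If the report repeats 2.6, readers will credit these comparisons with a protection that the described design does not provide.

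**Working it through.** The core of the point is a comparison of text. The protocol gives no figure on it to reproduce.

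**Step 1. Is there a contradiction?** Sections 2.1 and 5 say open. Section 2.6 says that four roles are blinded and sets an unblinding rule. No sentence limits open to some roles or reconciles the two.

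**Step 2. Which statement fits the treatments in 2.7?** A patient who takes a multi-herb decoction on top of S-1 is in a visibly different position from one who takes S-1 alone. The clinician who gives the decoction by syndrome also knows. Patient and clinician blinding therefore fails on the design as described.

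**Step 3. Which roles and outcomes are affected?**

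| Role or outcome | Can it be blinded as described? |
|---|---|
| Patients, treating clinicians | No |
| Data collectors, outcome assessors | Possible only if kept apart from treatment; the means are not described |
| IREC (imaging) | Yes, and section 3 says so |
| Symptom scores, KPS, subjective AE grading | Exposed, because the patient or clinician supplies the judgement |
| Laboratory-based AEs (blood counts, liver and kidney function) | Much less exposed |
| PFS | Partly protected by blinded IREC reading; deaths are objective |
| OS | Largely insensitive |

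**Step 4. How large could the effect be?** The documents cannot answer this. Section 2.12 gives a standard deviation of 9.59, but neither the outcome it belongs to nor a difference to detect. It therefore cannot be used to scale a bias on the symptom score.

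A purely hypothetical calculation shows the mechanism. Take about 58 evaluable patients per arm within one carcinoma type (64 × 0.9 = 57.6) and no true effect. Assume an expectation bias of *b* standard deviations; *b* is not taken from the documents. The two-sided 5% test then rejects with probability

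Φ(*b*√(58/2) − 1.96) + Φ(−*b*√(58/2) − 1.96), where √29 = 5.385.

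- *b* = 0: 0.025 + 0.025 = 0.05
- *b* = 0.2: Φ(−0.883) + Φ(−3.037) = 0.189 + 0.001 = 0.19
- *b* = 0.3: Φ(−0.344) + Φ(−3.576) = 0.365 + 0.000 = 0.37

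These values follow from the assumed *b* alone and are not an estimate for this trial.

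**The case against.** The best defence is that this is a condensed article and that dispensing by number ("the drugs corresponding to the randomly assigned drug number are given in the order of participants’ enrollment") is typical of masked supply, so a placebo decoction may exist and simply not be described. That stands to this extent: the absence of a placebo is inferred from the arm descriptions and is not declared. It does not remove the problem. If a placebo exists, the word open is wrong in two places; if none exists, section 2.6 is wrong. A drug number alone does not hide whether a patient takes a decoction.

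A reader might also infer more than the documents support:

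- **That the primary endpoint is unprotected.** Section 3 has the IREC read every participant's imaging blinded and rests the final evaluation on it. This largely settles whose call of progression counts, although 2.8.1 does not repeat it. What remains is indirect: withdrawal decisions under 2.10.2 and the occasion for unscheduled imaging lie with people who know the arm.
- **That only the IREC could be blinded.** An open-label trial can also mask a statistician, independent data collectors or those grading laboratory events.
- **That unblinding at an SAE destroys the blind.** Where patients and clinicians were never blind, it costs little, and disclosure after a death cannot alter that event. The rule does not say who is told, and nothing says that the IREC is. A sentence excluding the IREC is a precaution.
- **That an open add-on design is itself a fault.** It is legitimate; the fault is the claim made about it.

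**Conclusion.** The point holds as an internal contradiction with a practical consequence. Section 2.6 claims blinding of patients and treating clinicians that the described design does not have, and the symptom, KPS and subjective AE results would be presented with more protection than they have. PFS keeps partial protection through the IREC, so the primary comparison is not undermined on this ground.

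No numerical size can be given. The conclusion assumes that section 2.7 describes both arms fully on this point. The need to reconcile the text does not depend on that assumption, because the statements cannot all be true under either reading.

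**What to change.** Reconcile sections 2.1, 2.6, 2.7 and the Discussion. On the design as described:

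1. In 2.6, remove patients and clinicians from the blinded list. Call the trial open-label, with blinding limited to the IREC and any other role that can truly be masked, and say how each is masked.
2. In 2.8.1, state that the progression date for PFS is the one determined by the IREC, in line with section 3.
3. In 2.6, state that disclosure of allocation after an SAE does not reach the IREC.
4. Report the symptom, KPS and AE comparisons as open-label.

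If a masked placebo decoction does exist, describe it in 2.7 and remove the word open from 2.1 and the Discussion instead.

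The cost is wording only, since the IREC is already in place. The downside is a weaker claim for the subjective secondary outcomes.
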